**1. Background**

Fascioliasis is a disease caused by the infection of liver flukes of the species *Fasciola hepatica* and *F. gigantica*.It isa zoonotic disease that is of great veterinary importance and considerable public health significance worldwide. In humans, an infection with *Fasciola* spp. occurs through oral ingestion of metacercariae either through consumption of raw, undercooked or unwashed aquatic plants, or through drinking contaminated water (Mas-Coma, 2004). Chronic infections can lead to severe disabling diseases, including hepatic lesions, fibrosis and chronic inflammation of the bile ducts (Richter et al., 2002; Mas-Coma, 2004). An estimated 91 million people are at risk of fascioliasis mainly in the Andean countries of South America, Cuba, Western Europe, Egypt and the Islamic Republic of Iran (Keiser and Utzinger, 2005). It is estimated that between 2.4 and 17 million people are currently infected with *F. hepatica* and/or *F. gigantica* (WHO, 1995; Esteban et al., 2003). In some parts of Egypt human fascioliasis has become an important clinical problem and prevalence rates of 13-17% have been reported (Hammouda et al., 1995). High *F. hepatica/F. gigantica* prevalences have been reported in school aged children (Esteban et al., 2003).

There is no fascioliasis vaccine available and hence chemotherapy is the current mainstay for morbidity control of the disease. However, chemotherapy of fascioliasis relies on a single drug, namely triclabendazole (Egaten®) (Keiser et al., 2005). Although, triclabendazole has been routinely used for more than 2 decades in veterinary medicine, it is currently registered in only 4 countries to treat patients infected with *Fasciola* spp. (Keiser et al., 2005). Bithionol, emetine and dehydroemetine are still used for the treatment of fascioliasis, but all of these agents can cause serious adverse events (Chen and Mott, 1990; Apt et al., 1995).

Against this background, there is a pressing need for discovery and development of novel fasciocidal drugs. This is justified on the following three grounds. First, in the absence of a vaccine, and the challenges surrounding implementation of preventive measures such as access to clean water and improved sanitation and the difficulties in changing human behavior (i.e. thoroughly washing and cooking aquatic plants) control of food-borne trematodiasis in general and fascioliasis in particular rests on morbidity control. However, as mentioned above chemotherapy of fascioliasis relies on triclabendazole alone. Second, the dependence on a single drug for treatment and control of fascioliasis is an alarming situation, particularly in view of mounting evidence of drug resistance development. Triclabendazole resistance is already common in sheep and cattle (Keiser et al., 2005). Third, the development and delivery of new drugs – singly or in combination with drugs that have a different mechanism of action – is a key factor in enhancing therapeutic outcomes and prolonging the useful life-span of triclabendazole (White, 1999; Olliaro and Taylor, 2004).

In our previous study carried out between April and July 2007 in Egypt we found that a 3 day dose schedule of 80 mg artemether twice daily resulted in a cure rate of 35%. We would now like to follow up on this promising result and investigate the effect of slightly higher doses of artemether, namely 600 mg artemether in 3 divided doses 6 h apart. This treatment regimen has been used safely in the treatment of malaria (Nosten, 1994).

**2. Detailed research plan**

**2.1. Study aims**

To assess the safety and efficacy of oral artemether in Egyptian patients infected with *F. hepatica/ F. gigantica*

**3.2. Experimental design**

*Study area and patients*

The study will be carried out as a proof of concept open label trial in approximately 20 patients based on guidelines by Julius et al at a governorate of lower Egypt and will include a maximum of 18 patients (15 patients and an additional 3 to compensate for patients leaving the study voluntarily) with a parasitological-confirmed infection with *F. hepatica* and/or *F. gigantica*. We will include children (11 years and older) as *F. hepatica/F. gigantica* prevalences and morbidity are high in school age children.

*Patient inclusion criteria*

1.) Age 11-70 years, both sexes

2.) For married females, not pregnant, as assessed by the medical doctor last menstrual cycle, upon initial clinical assessment

3.) Absence of major systemic illnesses, as assessed by the medical doctor, upon initial clinical assessment

4.) Infection with *F. hepatica* and/or *F. gigantica* as confirmed by standard parasitological stool examination

5.) No known or reported hypersensitivity to artemether

6.) No known or reported history of chronical illness as cancer, diabetes, hypertension, chronic heart, liver or renal disease.

7.) Full clinical examination

8.) Written informed consent

*Patient exclusion criteria*

1.) Presence of any abnormal medical condition, judged by the medical doctor. If several patients experience serious adverse events the study will be stopped

2.) Severe liver disease of other etiology

3.) Recent history of anthelminthic drugs (triclabendazole, albendazole, bithionol, dehydroemetine, praziquantel within past 4 weeks)

4.) Attending other clinical trials during the study

5.) For females: pregnancy, lactation

Patient who were found with a *F. hepatica*/*F. gigantica* infection, but who were excluded from the study due to one or several of the above mentioned exclusion criteria will undergo a complete medical examination and will be provided a single oral dose of 10 mg/kg triclabendazole (Egaten®) and if necessary spasmolytic drugs according to standard procedures of the Ministry of Health and Population in Egypt.

*Baseline survey*

Medical history of patients participating in the study will be assessed with a standardized questionnaire, in addition to full clinical examination carried out by clinician. Blood samples will be collected for complete haemogram, including sedimentation rate, red, white and differential blood cell count, liver (alkaline phosphatase, alanine amino transferase, gamma glutamyltransferase, bilirubin) and kidney functions (serum urea and creatinine) as well as for diagnostic tests, which will be carried out in Egypt and Switzerland.

*F. hepatica* and/or *F. gigantica* infection intensity: Three stool samples of patients collected within 5 consecutive days will be examined utilizing the Kato Katz method Flotac, and the Formol-ether sedimentation technique simultaneously. A total of 9 Kato-Katz thick smears will be prepared (3 smears from each of the 3 stool specimen). Infection intensity (arithmetic mean egg count per gram of stool) will be calculated.

*Treatment*

As malaria is not present in the study area we will use an artemether monotherapy treatment regimen.

Artemether capsules (Artemidine®--50 mg/tablets) will be provided by Kunming pharmaceuticals. Artemidine® is manufactured according to international Good Manufacturing Practice (GMP) standards and fully licensed for human use as antimalarial treatment.

We will evaluate the effectiveness of oral artemether administered to 18 patients (15 patients and an additional 3 to compensate for patients leaving the study voluntarily) as a 3 dose treatment regimen closely mirroring a previously commonly used antimalarial treatment regimen: i.e. a three dose regimen with 600 mg artemether in 3 divided doses in intervals of 6 hours. This artemether treatment schedule has been used safely in a large number of patients (Nosten, 1994).

A spasmolytic drug will be administered one day before treatment with artemether and once daily within the period of artemether treatment.

All tablets will be administered in the presence of the investigator(s), and ingestion confirmed. This will be recorded with the time and date of closing. Subjects will be asked not to take any drugs other than those prescribed by the study medical team. After ingestion of artemether, the subjects will be observed for 1 hour to ensure retention of the drug. Vomiting within 1-hour post dosing will require re-dosing. The subjects will not allow more than one repeated dose. No re-administration will be needed for subjects vomiting after 1 hour.

*Morbidity monitoring*

Patients receiving artemether will be visited daily by the clinician during the period of drug administration. They will be kept for observation for at least 3 hours for any acute adverse events (AEs). If there is any abnormal finding, the study physicians will perform full physical examination on each individual and findings will be recorded. AEs within 24 hours of drug administration will be assessed. Those patients who report AEs will be examined carefully by the study physician and, when necessary, action will be taken (see appendix). Details of adverse experiences will be recorded by the medical doctors during the trial, including variables describing their incidence, onset, cessation, duration, intensity, frequency, seriousness, and causality (as determined by the physician), as well as any action taken (for grading of adverse events see appendix).

Follow-up after treatment will be on day 2 and 3 and 4-5 weeks later. In addition to clinical examination during follow-up periods, blood samples will be collected for complete haemogram, including sedimentation rate, red, white and differential blood cell count, liver (alkaline phosphatase, alanine amino transferase, gamma glutamyltransferase, bilirubin) and kidney functions (serum urea and creatinine).

Patients suffering from acute fasciolosis will be immediately treated with 10 mg/kg triclabendazole (Egaten®, Novartis) and spasmolytic drugs and excluded from the study.

Intensity of adverse events will be judged by the medial doctor as followed:

*Mild:* present but not required any interference.

*Moderate:* 1) present and required medication for symptomatic relief as requested by the affected people or 2) present and interfering with normal daily activities.

*Severe:* present and required medical intervention beyond symptomatic relief

Relationship of adverse events to the study medication will be determined. The probability of relation with treatment will be graded by the medical doctor. Changes in clinical signs and symptoms related to fascioliasis (nausea, abdominal pain, diarrhea, urticaria and pruritus) will be monitored.

*Endpoint parasitological stool survey and clinical evaluation*

*F. hepatica and/or F. gigantica*  infection intensity: 28 days after the last artemether dose has been administered patients stool samples will again be examined for the number of *F. hepatica* *and/or F. gigantica*  eggs in 3 different stool samples. Participants will be considered *F. hepatica* negative if no eggs have been found in 3 stool specimens analyzed by 3 Kato-Katz thick smears and Formol-Ether sedimentation technique taken from the same stool sample from each patient. Infection intensity (arithmetic mean egg count per gram of stool) will be calculated.

All patients will be treated with 10 mg/kg triclabendazole (Egaten®).

At the end point clinical evaluation blood samples will be collected for complete haemogram, including sedimentation rate, red, white and differential blood cell count, liver (alkaline phosphatase, alanine amino transferase, gamma glutamyltransferase, bilirubin) and kidney functions (serum urea and creatinine).

*Concomitant therapy*

All medications taken one month before and during the study period must be recorded with indication, dose regimen, date and time of administration.

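### The only stated pregnancy check covers married females, although pregnancy excludes every female and enrolment starts at age 11

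*Protocol*

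**What the plan says.** All the eligibility text is in the Protocol, section 3.2 (Experimental design).

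- Inclusion criterion 1 sets the population: "Age 11-70 years, both sexes". The paragraph on study area and patients says that school-age children are recruited on purpose.
- Inclusion criterion 2 sets the pregnancy assessment: "For married females, not pregnant, as assessed by the medical doctor last menstrual cycle, upon initial clinical assessment".
- Exclusion criterion 5 reads "For females: pregnancy, lactation". It has no marital limit and names no method.
- The general steps that apply to everyone are inclusion criterion 7 ("Full clinical examination"), exclusion criterion 1 ("Presence of any abnormal medical condition, judged by the medical doctor") and the baseline survey. In that survey, medical history "will be assessed with a standardized questionnaire, in addition to full clinical examination carried out by clinician". Blood is taken for haematology, liver and kidney tests, "as well as for diagnostic tests, which will be carried out in Egypt and Switzerland".
- The trial "will include a maximum of 18 patients", that is, 15 plus 3 to cover voluntary withdrawals.

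**The concern.** Criterion 2 is not silent about who is to be assessed. It names a group, and that group is smaller than the one exclusion criterion 5 protects. An investigator can follow criterion 2 to the letter and never ask an unmarried adolescent or adult about her last menstrual cycle. Read literally, the wording also leaves out divorced and widowed women.

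What is at stake is exposure during an unrecognised pregnancy. Treatment is 600 mg of artemether in three doses six hours apart, with a spasmolytic alongside. At the endpoint every patient also receives triclabendazole. The point needs no outside toxicity data, because the Protocol itself treats pregnancy as disqualifying. Eligibility criteria belong in a protocol, so a statistical analysis plan would not be expected to repair this.

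**Working it through.** The plan states no figure to reproduce. The check is a comparison of scope, followed by a simple bound on how many participants it could concern.

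**Step 1: set the two criteria side by side.**

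| | Inclusion criterion 2 | Exclusion criterion 5 |
|---|---|---|
| Who is covered | Married females | All females |
| Condition | Pregnancy | Pregnancy and lactation |
| Method | Doctor's assessment from the last menstrual cycle | None stated |
| When | Initial clinical assessment | Not stated |

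The criteria do not formally conflict, because a participant must satisfy both. The difference is that the rule covers all females while the method covers only some. Those left over are unmarried females who are post-menarchal and pre-menopausal. With entry from age 11, that group is within the intended population.

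**Step 2: look for another step that covers the remainder.** The visible Protocol was read from the Background to the appendices for any mention of pregnancy, lactation, menstruation, marital status or a pregnancy test.

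- Baseline survey: history questionnaire, examination, haemogram, liver and kidney function, and unspecified diagnostic tests. Pregnancy is not named.
- Morbidity monitoring and endpoint evaluation: clinical examination and the same haematology, liver and kidney tests. Pregnancy is not named.
- Appendix 1 form: the history block covers hypertension, diabetes and chronic illness. The form has no field for last menstrual period, pregnancy, lactation or marital status. Even the check on married women has no dedicated place to be recorded.

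No stated step closes the gap.

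**Step 3: bound the number of participants concerned.**

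- Maximum enrolment, from section 3.2: 15 + 3 = 18.
- Number entering without the stated assessment: between 0 and 18. The Protocol gives no mix of sex, age or marital status with which to narrow this.
- Illustration on assumed shares that are not in the documents: number = 18 × (share female) × (share of those unmarried and post-menarchal).
  - Low: 18 × 0.30 × 0.20 = 1.08
  - High: 18 × 0.60 × 0.50 = 5.40

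On those assumptions, about 1 to 5 of 18 participants would enter without the check. This counts people not assessed. It does not count pregnancies.

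**The case against.** The strongest reply is that exclusion criterion 5 already protects everyone. A doctor must satisfy it for each female before dosing, with a history and an examination in which to do so. Other exclusions, such as other liver disease or recent anthelminthic treatment, also name no method, so leaving the method to the doctor is the document's normal style. The questionnaire's content and the diagnostic tests are unspecified and might include pregnancy.

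Part of this stands. A known pregnancy is excluded whatever the marital status, and a careful doctor may well ask. It cannot be shown that unmarried participants would in practice go unassessed. But the other exclusions do not come with a method confined to a subgroup. Here the Protocol states who is to be assessed and stops at married females, which a site may reasonably read as not requiring the question of others. The Protocol offers no rationale for using marriage as a proxy, and exclusion criterion 5 does not use it.

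Two further objections are fair. The numerical range rests on assumed shares and should carry no weight in judging importance. A last-menstrual-cycle assessment also depends on self-report and will not reliably find every early pregnancy, so extending it aligns the scope without guaranteeing detection.

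**Conclusion.** The point holds. The only pregnancy assessment stated in the visible Protocol is limited to married females, while the exclusion it serves covers all females and enrolment begins at 11. Followed as written, an unmarried post-menarchal participant with an unrecognised pregnancy could be dosed.

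It is a modest but real safety point that the sponsor should correct. No endpoint, sample size or estimate depends on it. The firm bound on participants affected is 0 to 18; the narrower figure of about 1 to 5 is illustration only.

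The conclusion rests on the visible text. The pages before the Background were not available, and the questionnaire and the diagnostic tests are not described. If either includes a pregnancy check for all females, the gap is one of wording only.

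**What to change.** Reword inclusion criterion 2 along these lines: *For all females of childbearing potential (post-menarche, pre-menopause), regardless of marital status: not pregnant, as judged by the medical doctor from the last menstrual cycle at the initial clinical assessment.* Add fields for last menstrual period, pregnancy status and lactation status to the Appendix 1 form, so that both parts of exclusion criterion 5 are asked about and recorded.

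Deleting the word for marital status alone is not enough. The assessment would then apply to all females aged 11 to 70, including those before menarche or after menopause.

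The cost is one reworded criterion and a few form fields. The drawback is some sensitive screening questions for unmarried participants and minors. A pregnancy test before dosing would be a stronger safeguard if the sponsor wants to go beyond self-report. With at most 18 participants, the number of tests would be small.

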**Appendix 1: Personal data and clinical examination form**

Date : _____/______/ 2007 (jj/mm)

| Name |  |
| --- | --- |
| First name |  |
| Address |  |
|  |  |
| Date of birth |  |

| Temperature | °C |
| --- | --- |
| Weight | kg |
| Height | cm |
| Blood pressure | # / # mm Hg |
| Pulse | # / min |

| **History** |  |
| --- | --- |
| History of hypertension |  yes  no |
| History of diabetes |  yes  no |
| History of chronic illnesses |  yes  no |

| **Clinical picture** |  |
| --- | --- |
| Intermittent fever |  yes  no |
| Headache |  yes  no |
| Nausea |  yes  no |
| Vomiting* |  yes  no |
| Diarrhea |  yes  no |
| Dull Abdominal pain |  yes  no |
| Collical pain |  yes  no |
| Vertigo |  yes  no |
| Malaise and weight loss |  yes  no |
| Constipation |  yes  no |
| Pruritus |  yes  no |
| Urticaria |  yes  no |
| Jaundice |  yes  no |
| Cough and chest pain |  yes  no |
| Sweating, dizziness |  yes  no |

*If yes, give antiemeticum

| **Physical examination** |  |
| --- | --- |
| Hepatomegaly |  |
| Abdominal tenderness |  |
| Splenomegaly |  |
|  |  |

| Anthelminthic treatment in the last 4 weeks |  | Other medication |
| --- | --- | --- |

**Parasitological stool survey** (Fasciola eggs/gram)

| Stool sample | Formal Ether sedimentation | Kato Katz 1 | Kato Katz 2 | Kato Katz 3 |
| --- | --- | --- | --- | --- |
| 1 |  |  |  |  |
| 2 |  |  |  |  |
| 3 |  |  |  |  |
|  |  |  |  |  |

| **Hematology and biochemistry** |  |  |
| --- | --- | --- |
| Erythrocyte sedimentation rate |  | |
| Red blood cell count |  | |
| White blood cell count |  | |
| Platelets |  | |
| Differential blood cell count |  | |
| Alkaline phosphatase |  | |
| Alanine amino transferase |  | |
| Gamma glutamyltransferase |  | |
| Bilirubin |  | |
| Urea |  | |
| Creatinine |  | |

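### Fascioliasis symptoms are recorded before treatment only as yes/no while adverse events are graded, so worsening of a complaint already present cannot be told from its persistence

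*Protocol*

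**What the plan says.** Section 2.1 makes safety, with efficacy, the aim of the study. Section 3.2 describes an open-label proof-of-concept trial in one treated group of 15 patients plus 3 to cover withdrawals.

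- **Symptoms as disease signs.** Morbidity monitoring says: "Changes in clinical signs and symptoms related to fascioliasis (nausea, abdominal pain, diarrhea, urticaria and pruritus) will be monitored". It gives no scale for change.
- **Adverse-event intensity.** The same subsection sets three grades. Mild is "present but not required any interference". Moderate depends on requested symptomatic medication or on limits to ordinary activity. Severe is "present and required medical intervention beyond symptomatic relief". None refers to the state before treatment.
- **Other adverse-event data.** The physicians record "incidence, onset, cessation, duration, intensity, frequency, seriousness, and causality (as determined by the physician"), and "The probability of relation with treatment will be graded by the medical doctor".
- **Baseline.** The Baseline survey says: "Medical history of patients participating in the study will be assessed with a standardized questionnaire, in addition to full clinical examination carried out by clinician". The only symptom form shown, Appendix 1, lists all five symptoms (abdominal pain as "Dull Abdominal pain" and, separately, colicky pain). Each has a yes/no answer and no severity field, and the form carries one date line.
- **Routine spasmolytic.** Under Treatment: "A spasmolytic drug will be administered one day before treatment with artemether and once daily within the period of artemether treatment".

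Follow-up visits are planned on days 2 and 3 and at 4-5 weeks. Only the heading of Appendix 2, on adverse-event grading, is visible.

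**The concern.** Nausea and abdominal pain are disease symptoms here, and they are also complaints a patient might well report after dosing. The list of permitted medication allows antiemetics against nausea and spasmolytics for symptoms of parasite expulsion, so the protocol itself expects such complaints on treatment.

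With no control arm, the patient's own state before treatment is the only reference for separating disease from drug. That reference is recorded on a two-level item, while events after dosing are graded on three levels. Without a baseline grade, two opposite errors are possible: an unchanged complaint is recorded as a mild adverse event, or a complaint that became worse after artemether is set aside as part of the fascioliasis. The physician deciding between them knows the treatment and has no recorded grade to compare with.

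The gap lies in data collection. A later analysis plan could define treatment-emergent events, but it could not recover a baseline severity that was never recorded.

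**Working it through.** The protocol gives no figure on this point, so there is none to reproduce. The check compares what the form can hold with what the monitoring statement requires.

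**Inputs.** Three grades (Morbidity monitoring) plus absence give four possible states per symptom. The Appendix 1 item has two. There are 15 + 3 = 18 patients (section 3.2).

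**Step 1: yes/no at both times.** Four states before and four after give 4 × 4 = 16 pairs.

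| Before / after | Pairs of grades merged |
| --- | --- |
| no / no | 1 |
| no / yes | 3 |
| yes / no | 3 |
| yes / yes | 3 × 3 = 9 |

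The total is 1 + 3 + 3 + 9 = 16. The yes/yes cell holds 3 unchanged, 3 worse and 3 better pairs, and the form cannot separate them.

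**Step 2: yes before, graded after.** This is the case when the complaint after dosing is recorded as an adverse event.

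| Grade after dosing | Possible grade before | What can be concluded |
| --- | --- | --- |
| Mild | mild, moderate or severe | unchanged or better; worsening excluded |
| Moderate | mild, moderate or severe | worse, unchanged or better |
| Severe | mild, moderate or severe | worse or unchanged |

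The doubt about worsening is confined to moderate and severe complaints, the ones that matter most for safety. A mild complaint that was also present before could be recognised as not treatment-emergent from the yes/no item alone, if a rule told the physician to do so. No visible text does.

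**Step 3: what yes/no data can still show.** Appearance and disappearance are measurable. By the exact two-sided sign (McNemar) test, if all k patients who change move the same way, p = 2 × 0.5^k:

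- k = 5: p = 2 × 0.5^5 = 0.0625
- k = 6: p = 2 × 0.5^6 = 0.03125

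At an assumed two-sided level of 0.05, which the protocol does not state, 6 of the 15 to 18 patients would be enough. Change in presence can be studied; only change in severity is lost.

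**Step 4: does recorded onset close the gap?** Only in part. Onset can show that a complaint began before dosing, but it carries no earlier grade. If onset before dosing excludes a complaint, pain going from mild to severe may be excluded with it. If it does not, unchanged pain may be listed as an event.

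**Step 5: timing of the baseline reading.** Every patient receives a spasmolytic from the day before artemether. The baseline survey is described ahead of treatment, but no text places the symptom reading before that first dose. The moderate grade also depends partly on requested symptomatic medication, so routine cover may influence the grade itself.

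**Size.** The number of misclassified complaints lies between zero and the number of patients who have the symptom both at entry and after dosing. The protocol gives no figure for the latter.

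**The case against.** The strongest objection is that *present* stands in an intensity scale. It grades something already judged to be an adverse event and does not define what becomes one. Onset and causality are recorded separately, so a complaint that began before dosing can be identified and judged unrelated. This stands. A reader might infer that pre-existing complaints **are** counted as drug events; the document does not say so. Nor would pain that became severe vanish, since it could be recorded as a severe event with its onset and the action taken. What would be missing is the grade it started from.

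Second, a reader might infer that change cannot be measured at all. Step 3 shows that this is wrong.

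Third, one might multiply 15 patients by an assumed entry frequency of 20%, 40% or 60% to get 3, 6 or 9 false events. The frequencies are assumptions, and the product also supposes that every persisting complaint is logged as an adverse event despite recorded onset and causality. The documents support neither.

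Fourth, the body of Appendix 2 is not visible and may hold a definition or a baseline column, and the questionnaire and clinical examination may capture more than Appendix 1. The unseen appendix cannot be held against the plan. The visible text does not describe either the questionnaire or the examination as grading symptoms.

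Fifth, a counting rule for treatment-emergent events is often left to the analysis plan. That is fair, and the absence of the rule alone would be no finding. The form, however, is fixed in the protocol.

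Last, early relief of pain under the spasmolytic might be mistaken for an artemether effect. The protocol makes no claim of early relief, and its 4-5 week visit falls outside the routine spasmolytic period. The only part that remains is to place the baseline reading before the first spasmolytic dose.

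**Conclusion.** The point holds in limited form. The protocol undertakes to monitor change in five symptoms and grades adverse events on three levels, but the symptom form it shows has two levels and no severity. Of the 16 possible before/after pairs of states, 9 fall into one yes/yes cell in which worse, unchanged and better cannot be separated. When the later complaint is graded, the doubt about worsening remains for moderate and severe complaints. The decision between disease and drug then rests on unblinded judgement without a recorded baseline grade or a control arm.

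This is a weakness in the safety record that is cheap to remove. It does not show that the adverse-event count will be wrong, and no size can be given for any error. The conclusion assumes that Appendix 1 is the baseline symptom record and that neither the questionnaire nor the unseen part of Appendix 2 holds a graded pre-treatment score. If either does, the protocol need only refer to it and the point largely falls away.

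**What to change.** 1. In Appendix 1, replace yes/no for the symptom items with none, mild, moderate or severe, using the intensity definitions already given under Morbidity monitoring.
2. Complete the list at baseline before the first spasmolytic dose, on days 2 and 3, and at weeks 4-5, with the visit marked on each sheet.
3. State in the protocol that symptoms which are new or of higher grade than at baseline are reported as treatment-emergent. Onset and causality continue to be recorded as planned.

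The spasmolytic itself is unchanged, and all these visits are already scheduled. The cost is a short wording change, a revised form and slightly longer form completion.

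### Flotac is used at baseline but is missing from the day-28 cure rule, and the entry rule names no method, so the cure rate can be biased upward by an amount the protocol does not fix

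*Protocol*

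**What the plan says.** Four places in the protocol bear on how infection and cure are established.

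- **Entry** (section 3.2, *Patient inclusion criteria*): infection must be present "as confirmed by standard parasitological stool examination". No method is named.
- **Baseline** (section 3.2, *Baseline survey*, under infection intensity): "Three stool samples of patients collected within 5 consecutive days" are to be "examined utilizing the Kato Katz method Flotac, and the Formol-ether sedimentation technique simultaneously". On Kato-Katz the text is explicit: "A total of 9 Kato-Katz thick smears will be prepared (3 smears from each of the 3 stool specimen").
- **Day 28** (section 3.2, *Endpoint parasitological stool survey and clinical evaluation*): stools are examined again for "eggs in 3 different stool samples", and a participant is "negative if no eggs have been found in 3 stool specimens analyzed by 3 Kato-Katz thick smears and Formol-Ether sedimentation technique". Flotac is not mentioned.
- **Record form** (Appendix 1): for each of three samples the columns are "Formal Ether sedimentation | Kato Katz 1 | Kato Katz 2 | Kato Katz 3". There is no Flotac column.

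Mean eggs per gram is to be calculated at both time points, without saying which method's counts enter.

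**The concern.** Three methods are applied before treatment, but only two decide who is cured. When a patient is positive if any method shows eggs, leaving a method out cannot make the work-up more sensitive. Any detection lost in this way is counted as cure.

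Two features of this trial make that hard to correct later. It is open label with no control arm, so a missed infection cannot be told apart from a drug effect. All patients receive triclabendazole at the endpoint, so a missed failure cannot be established by later stool testing. The cure rate is also the figure that will be set beside the 35% reported from the earlier study in section 1. With about 15 evaluable patients, one misclassified patient moves it visibly.

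**Working it through.** **Check of the protocol's own figure.** 3 specimens × 3 smears = 9 Kato-Katz smears at baseline, as stated. No sensitivity, target cure rate or power is given, so there is nothing else to reproduce.

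**Side by side.**

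| Item | Entry rule | Baseline survey | Cure rule, day 28 | Appendix 1 form |
|---|---|---|---|---|
| Specimens | not stated | 3 | 3 | 3 |
| Kato-Katz | not stated | 9 smears | 3 smears, most naturally per specimen (9) | 3 × 3 = 9 cells |
| Formol-ether | not stated | yes | yes | yes |
| Flotac | not stated | yes | not named | no column |

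**What follows depends on Flotac's unstated role.**

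1. *Flotac neither decides entry nor is read at day 28.* Entry and cure rest on the same two methods. There is no mismatch, only the ordinary imperfect sensitivity of those methods.
2. *Flotac can decide entry.* Suppose k of 15 patients enter on Flotac alone, and each, while still infected, goes undetected by the other two methods at day 28 with probability u. Under an inactive drug they add k × u / 15 to the cure rate. For k = 1 this lies between 0 (u = 0) and 1/15 = 6.7 points (u = 1). With all 18 patients evaluable the upper figure is 1/18 = 5.6 points. The documents give neither k nor u.
3. *Flotac is read at day 28 but not counted.* A patient with eggs seen only on Flotac still meets the written cure rule.

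**Size in case 3.** Let c be the true cure rate, Se2 the sensitivity of Kato-Katz plus Formol-ether for an uncured patient, and f the share of infections missed by those two that Flotac would find. All three are assumptions; 35% is borrowed from section 1 only as an illustration.

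- Sensitivity with Flotac: Se3 = 1 − (1 − Se2)(1 − f)
- Apparent cure rate: c + (1 − c)(1 − Se)
- Excess from not counting Flotac: (1 − c)(1 − Se2) f, which is never negative

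| c | Se2 | f | Two methods | Three methods | Excess | Patients of 15 |
|---|---|---|---|---|---|---|
| 35% | any | 0 | same | same | 0 | 0 |
| 35% | 90% | 50% | 0.35 + 0.65 × 0.10 = 41.5% | 0.35 + 0.65 × 0.05 = 38.25% | 3.25 points | 0.5 |
| 35% | 70% | 75% | 0.35 + 0.65 × 0.30 = 54.5% | 0.35 + 0.65 × 0.075 = 39.9% | 14.6 points | 2.2 |
| 20% | 70% | 75% | 0.20 + 0.80 × 0.30 = 44.0% | 0.20 + 0.80 × 0.075 = 26.0% | 18.0 points | 2.7 |

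Over c = 20–50%, Se2 = 70–95% and f = 0–75%, the excess runs from 0 to 18 points.

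**The case against.** The strongest reply is that Flotac may play no part in efficacy. It is named once, under baseline infection intensity. The entry rule asks only for a standard stool examination, and the form's columns match the cure rule. On that reading entry and cure already agree. This reply stands as far as it goes: the documents do not show that anyone can enter on Flotac alone. They do not exclude it either. The form is weak evidence because it carries a pre-printed 2007 date, the year of the earlier study, and may have been carried over. Nor does it help that stools are to be examined again at day 28: if that includes Flotac, the cure rule ignores the result.

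A reader might also go further than the text allows in several ways.

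- *That infection is established by three methods and the cure rate is therefore inflated.* The entry rule names no method and no sensitivity is given. The bias is possible and one-directional, but not demonstrated.
- *That each Flotac-only entrant adds a full 6.7 points, and three add 20.* This needs such patients to be admitted and then to stay undetected by the other two methods on fresh specimens at day 28. Nothing in the protocol indicates how many there would be.
- *That day 28 uses three Kato-Katz smears in all, which would cost much more sensitivity.* The wording permits this, but the reference to the same stool sample, the repeat of the examination and the nine cells on the form all point to three per specimen. Putting a number on it would need smear weights and egg densities that the documents do not give, and Formol-ether would have to be included.
- *That a patient shedding F. gigantica eggs could be called cured because the rule says F. hepatica negative.* The heading and the preceding sentence cover both species, the rule requires that no eggs be found, and the form counts Fasciola eggs. This is shorthand.
- *That eggs per gram before and after rest on different slides.* The same sentence is used at both times, and no text assigns different slides.

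One might finally leave the matter to a statistical analysis plan. Such a plan could say that Flotac does not count. It could not supply day-28 readings that were never made, or change how patients were admitted.

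**Conclusion.** The mismatch is real: Flotac belongs to the baseline work-up but not to the cure rule or the form, and the entry rule does not settle which methods count. If Flotac can decide entry, or is read at day 28 and disregarded, the cure rate can be raised and cannot be lowered. The direction follows from the any-positive logic alone. The size is not fixed by the documents: it is zero if Flotac adds nothing to the other two methods, and 0 to 18 points is a range under assumed values, not an estimate. The point should be fixed before enrolment because it concerns a stated endpoint rule and costs almost nothing to settle. A proven distortion of the result has not been shown.

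**What to change.** Use the same methods and the same smear count for entry and for cure, in one of two ways.

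1. **No cost.** Base parasitological confirmation at entry, the cure-rate denominator and cure on three specimens, each with three Kato-Katz smears (nine in total) plus Formol-ether, and label Flotac exploratory. This takes a few sentences. It removes the mismatch, though infections missed by both retained methods would still count as cures.
2. **Small cost.** Repeat Flotac at day 28 and add it to the cure rule and the form. This means 3 × 15 = 45 to 3 × 18 = 54 further readings with a method already in use, plus one form column.

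In the same sentence, three clarifications are worth making; they are not separate errors. State three smears per specimen, nine in total. Say that no Fasciola eggs of either species were found. Compute eggs per gram from the same set of Kato-Katz smears at both time points.
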